### Sample size

We aim to recruit a total of 120 participants, evenly distributed across three intervention groups, with 40 participants in each group. The determination of this sample size is based on projected improvements in key outcome measures, including the Western Ontario and McMaster Universities Osteoarthritis Index (WOMAC) for pain and physical function, as well as the physical component summary of the SF-36 health survey. Our calculations are informed by the findings from relevant randomized controlled trials (RCTs) that have utilized active control conditions, which provide a robust basis for estimating the anticipated treatment effects. This sample size is anticipated to provide sufficient statistical power to detect meaningful differences in outcomes between the intervention groups while accounting for the within-study variability.

The sample size was calculated using G*Power software (version 3.1) for a one-way analysis of covariance (ANCOVA) to handle the three-group comparison, adjusting for baseline values of the primary outcome (change in WOMAC score at week 12). Key statistical parameters were determined based on findings from relevant randomized controlled trials utilizing active controls, specifically studies by Hu et al. (44) and Ye et al. (45). Effect Size (f): Given the large and robust improvements in proprioception and WOMAC function scores (*p* < 0.05) consistently reported in these studies, we anticipated a large between-group effect size of *f* = 0.32. This corresponds to an expected mean difference of approximately 5.0 points with a common standard deviation (SD) of 9.0 points. Significance Level (α): Set at 0.05 (two-tailed). Statistical Power: Set at 80% (0.80).We are conservatively factoring in a 15% dropout rate to ensure the study retains sufficient statistical power. This adjustment helps to maintain the robustness of our findings even if a portion of the participants withdraw from the study.

In the event that the dropout rate exceeds our projected figures, we plan to perform a reassessment of the statistical power to ascertain the necessity of enlisting additional participants. This reassessment is crucial to ensure that the study maintains adequate power to detect the intended treatment effects. Moreover, if it is determined that an increased sample size is essential for enabling robust comparisons among participant subgroups and for ensuring equitable group dynamics, we will undertake a reevaluation of the sample size. This process is integral to preserving the methodological integrity of the study and to substantiating the generalizability of our findings.

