### Enrollment and the informed consent process

Participants are enrolled in groups of 40 to ensure adequate sample sizes for each intervention arm. Baseline assessments are conducted for pre-screened participants three weeks prior to intervention commencement to secure an eligible cohort. Informed consent is obtained by the principal investigator or study coordinator before any data collection. Prospective participants are fully informed about the study, including objectives, procedures, risks, and benefits, and provide written consent.

Following informed consent, participants undergo a final eligibility verification. Those confirmed eligible are randomized into one of the three groups: Tai Chi, Baduanjin, or health education, using a computer-generated sequence. This ensures balanced group assignment and maintains the trial's integrity. A total of 120 participants will be randomized, with 40 in each group, providing sufficient statistical power to detect meaningful differences.

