### Analysis

The primary outcomes for this study are defined as the changes from baseline to Week 12 in the three WOMAC subscales: Pain, Stiffness, and Physical Function. The primary analysis will be conducted using an intention-to-treat approach, where all participants are analyzed in the group to which they were randomized, without adjustment for covariates, and with missing 12-week outcomes imputed as no change. Secondary analyses will adjust for baseline characteristics that differ significantly by treatment group, including gender, initial pain severity, medication use, disease duration, and the number of chronic conditions.

Changes in knee pain at weeks 24 and 48, along with all other outcomes, are considered secondary and will be analyzed in the same manner as the primary outcome. We will also perform a longitudinal analysis across all four time points to identify potential time trends and interactions between treatment effects and time. These analyses will utilize mixed-effects models with random intercepts for participants and fixed effects for time, considering autoregressive structures for residual errors.

To handle missing values, we will employ multiple imputation techniques under the assumption of missing at random (MAR). Given the potential for early dropout due to poor outcomes, we will also explore models that account for missing not at random (MNAR) based on informative dropout assumptions. As part of our sensitivity analyses for missing data, we will consider Bayesian models that can incorporate prior assumptions about the non-ignorable missing data mechanisms.

All statistical tests will be two-tailed, with a significance level set at *p* < 0.05. We will conduct both individual time-point analyses and longitudinal analyses to provide a comprehensive understanding of the treatment effects over time.

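### The planning effect size f = 0.32 does not follow from the stated 5.0-point difference and SD of 9.0: on the natural reading those figures give f of 0.23 to 0.26 and omnibus power of about 51–64%, not 80%

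*Protocol article*

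**What the plan says.** The Sample size section of the protocol article gives these planning figures:

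- **Enrolment:** "We aim to recruit a total of 120 participants, evenly distributed across three intervention groups, with 40 participants in each group".
- **Test:** the calculation was done in G*Power "for a one-way analysis of covariance (ANCOVA) to handle the three-group comparison", adjusting for baseline. The outcome is the change in WOMAC score at week 12.
- **Effect size:** "we anticipated a large between-group effect size of *f* = 0.32".
- **Translation into points:** "This corresponds to an expected mean difference of approximately 5.0 points with a common standard deviation (SD) of 9.0 points".
- **Error rates and losses:** two-tailed alpha of 0.05, power of 80%, and 15% dropout.

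No baseline–outcome correlation, no pattern for the three means and no specific WOMAC subscale is attached to the 5.0 and 9.0.

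Two other sections bear on this. Enrollment and the informed consent process describes 40 per group as "providing sufficient statistical power to detect meaningful differences". The Analysis section specifies a primary analysis by intention to treat, "without adjustment for covariates", with missing week-12 outcomes imputed as no change.

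**The concern.** Cohen's f for a one-way layout is fixed by the group means and the common SD. Once a difference and an SD are stated, only the position of the remaining arm is left free. A 5.0-point spread with SD 9.0 looked too small to produce f = 0.32 wherever that arm lies.

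The sentence matters because it is the only place where the planned effect is expressed in WOMAC points. A reader will take from it that the trial has 80% power for a 5-point difference. If that is wrong, a non-significant result will be judged against a power claim the trial does not have.

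**Working it through.** **Inputs**, all from the Sample size section: three equal arms, 120 enrolled, f = 0.32, difference 5.0, SD 9.0, alpha 0.05, power 80%, dropout 15%. Evaluable participants: 120 × 0.85 = 102. The one assumption is that 5.0 is the largest difference between any two arms.

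**1. Reproduce the plan's N from f = 0.32.** Power comes from the noncentral F distribution with λ = f²·N, numerator df 2 and denominator df N − 4 (three groups, one covariate). The smallest N giving 80% is 98, or 99 if balanced. Then 99/0.85 = 116.5, so 117 enrolled; 120 is consistent with this. At N = 102, λ = 0.32² × 102 = 10.44 and power is 82%. At N = 120 it is 88%. This step is sound.

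**2. Derive f from 5.0 and 9.0.** f = (SD of the group means, divisor 3) / 9.0.

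- Two arms equal, means 0, 5, 5: √(16.667/3) = 2.357, and 2.357/9 = 0.262.
- Third arm midway, means 0, 2.5, 5: √(12.5/3) = 2.041, and 2.041/9 = 0.227.

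For a fixed range of 5.0 these are the extremes, so 0.32 is out of reach. The two-group shortcut, half of 5/9, gives 0.278 and does not reach it either. Using divisor 2 instead of 3 for means 0, 5, 5 gives √(16.667/2)/9 = 0.321. That may be the origin of the figure, but this is conjecture, and it is not the f that G*Power uses.

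**3. Power on the stated difference and SD.**

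| f | Power, 102 evaluable | Power, all 120 | Evaluable N for 80% |
|---|---|---|---|
| 0.32 (as planned) | 82% | 88% | 98 |
| 0.262 (two arms equal) | 64% | 72% | 144 |
| 0.227 (third arm midway) | 51% | 59% | 191 (192 balanced) |

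**4. What f = 0.32 requires.** The SD of the means must be 0.32 × 9 = 2.88.

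- At SD 9.0, the difference is 2.88 × 3/√2 = 6.1 points (two arms equal) or 2.88 × √6 = 7.1 points (evenly spaced).
- At a difference of 5.0, the SD is 2.357/0.32 = 7.4 or 2.041/0.32 = 6.4.

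**5. Correlation needed if 9.0 is an SD before baseline adjustment.** Adjustment turns f into f/√(1 − ρ²). Setting this to 0.32 gives ρ = √(1 − (0.2619/0.32)²) = 0.57 for two arms equal, and ρ = √(1 − (0.2268/0.32)²) = 0.71 for the third arm midway.

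**6. Effect of the planned imputation.** Suppose 15% are missing in each arm, unrelated to outcome, and set to no change. Differences shrink by 0.85, and the within-arm variance is at least 0.85 × 81. Hence λ ≤ 120 × 0.85² × f²/0.85 = 102·f². Keeping all 120 in the analysis this way does not recover the power lost to dropout, and 51–64% is roughly a ceiling.

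**The case against.** **The pattern of means is not stated.** The protocol speaks of an expected mean difference and does not say that it is the largest. If 5.0 is one exercise arm against education and the other exercise arm does better, means of 0, 5 and 6.8 at SD 9.0 give f = √(24.83/3)/9 = 0.32, and the plan agrees with itself. This stands as a limit on the claim: the figures disagree on the natural reading, not on every conceivable one. But the protocol gives no such pattern.

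**The sizing is for an ANCOVA.** Baseline adjustment does raise f, and a correlation of 0.57 to 0.71 would be enough. But none is stated, f is tied directly to the common SD of 9.0, and the primary analysis is unadjusted. A related escape is that 9.0 is the SD of a raw score while the outcome is change, whose SD would be 9√(2(1 − ρ)). Reaching 7.4 or 6.4 then needs ρ = 1 − (7.37/9)²/2 = 0.66 or 1 − (6.38/9)²/2 = 0.75. That is not stated either.

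**The calculation that fixes N is correct.** This stands in full. A reader might infer that 120 is a miscalculated sample size. It is not: f, alpha, power, dropout and N agree with one another.

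**Pairwise power.** A reader might also infer that the protocol misstates its power for the Bonferroni comparisons. For 5.0 and 9.0 at alpha 0.05/3 that power is about 44% (34 per arm) to 52% (40 per arm). But the 80% is claimed only for the three-group test, so these figures are context and contradict nothing written.

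**Stiffness.** It is tempting to say that an SD of 9 is nearly impossible on a 0–20 subscale, where a score's SD cannot exceed 10. The outcome is change, which can run from −20 to 20, so that bound does not apply.

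**Conclusion.** The sentence translating f = 0.32 into 5.0 points at SD 9.0 is wrong as written, on the natural reading that 5.0 is the largest difference between arms. Those figures give f = 0.227 to 0.262. Omnibus power is then about 51–64% with 102 evaluable and 59–72% with no dropout, against the stated 80%. The assurance of adequate power in the enrolment section is therefore unsupported for a 5-point difference.

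The result rests on three equal arms, 9.0 as the SD that the primary analysis faces, and 15% dropout for the lower range. An unstated pattern of means or an unstated correlation could reconcile the numbers, but the protocol supplies neither, and its unadjusted primary analysis forgoes the gain from baseline adjustment. The error lies in the stated detectable difference, not in the derivation of 120 from f.

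**What to change.** Keep 120 and correct the Sample size section in one of three ways:

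1. **Keep f = 0.32 and 80% power.** State that at SD 9.0 this means a largest difference of about 6.1 points (two arms equal) to 7.1 points (evenly spaced).
2. **Keep 5.0 and 9.0.** State omnibus power of about 51–64% with 102 evaluable, and reword the power statement in the enrolment section to match.
3. **Rely on baseline adjustment.** State the assumed correlation with its source (about 0.57 if two arms are equal, about 0.71 if the third is midway) and make the primary analysis in the Analysis section baseline-adjusted.

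In each case, name the WOMAC subscale and the pattern of means that the figures refer to.

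The first two options cost only rewording and a less favourable stated difference or power. The third also changes the primary analysis. The protocol says recruitment had not begun at submission, so that change can be made before any outcome data exist. None of the options needs more participants. By contrast, 80% power on 5.0 and 9.0 without adjustment would take 144/0.85 = 170 to 192/0.85 = 226 enrolled.

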### Analysis

The primary outcomes for this study are defined as the changes from baseline to Week 12 in the three WOMAC subscales: Pain, Stiffness, and Physical Function. The primary analysis will be conducted using an intention-to-treat approach, where all participants are analyzed in the group to which they were randomized, without adjustment for covariates, and with missing 12-week outcomes imputed as no change. Secondary analyses will adjust for baseline characteristics that differ significantly by treatment group, including gender, initial pain severity, medication use, disease duration, and the number of chronic conditions.

Changes in knee pain at weeks 24 and 48, along with all other outcomes, are considered secondary and will be analyzed in the same manner as the primary outcome. We will also perform a longitudinal analysis across all four time points to identify potential time trends and interactions between treatment effects and time. These analyses will utilize mixed-effects models with random intercepts for participants and fixed effects for time, considering autoregressive structures for residual errors.

To handle missing values, we will employ multiple imputation techniques under the assumption of missing at random (MAR). Given the potential for early dropout due to poor outcomes, we will also explore models that account for missing not at random (MNAR) based on informative dropout assumptions. As part of our sensitivity analyses for missing data, we will consider Bayesian models that can incorporate prior assumptions about the non-ignorable missing data mechanisms.

All statistical tests will be two-tailed, with a significance level set at *p* < 0.05. We will conduct both individual time-point analyses and longitudinal analyses to provide a comprehensive understanding of the treatment effects over time.

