**Methods/design:**

A single-centre, 48-week, comparative-effectiveness randomised controlled trial comparing Tai Chi, Baduanjin and health-education programme will be conducted at Zhongshan Hospital of Traditional Chinese Medicine. Eligible participants consists of adults ≥60 years of age with symptomatic and radiographic knee OA. Participants will be randomly assigned (1:1:1) using a computer-generated randomization sequence to one of three groups: (1) Tai Chi training, 5 sessions per week (60 min each) for 12 weeks; (2) Baduanjin training, 5 sessions per week (60 min each) for 12 weeks; or (3) health-education, 1 session per week (60 min each) for 12 weeks. Outcome assessors will be blinded to group allocation. The primary outcomes are the pain, stiffness and physical function subscales of the Western Ontario and McMaster Universities Osteoarthritis Index (WOMAC). Secondary outcomes include the Berg Balance Scale, 6 min walk test and SF-36 quality-of-life assessment. All measures will be assessed at weeks 12, 24 and 48.

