## Statistical analysis

All statistical analyses will be performed using SPSS Statistics version 26.0 (IBM Corp). Continuous variables will be first assessed for normality using the Shapiro–Wilk test and for homogeneity of variance using Levene's test. Data presenting a normal distribution will be expressed as mean ± standard deviation (SD). For comparisons among the three groups, one-way Analysis of Variance (ANOVA) will be used. If the ANOVA indicates a significant difference, *post-hoc* pairwise comparisons will be conducted using the Bonferroni correction to adjust for multiple testing. Non-normally distributed variables will be presented as median (interquartile range, IQR) and analyzed using the Kruskal–Wallis H test, followed by Dunn's test with Bonferroni correction for pairwise comparisons if significant. Categorical variables will be expressed as frequencies (percentages) and compared using the Chi-square test or Fisher's exact test where expected cell counts are less than 5.

For the primary outcome (change in clinical scores from baseline to post-intervention), repeated measures ANOVA will be employed, with Group as the between-subject factor and Time as the within-subject factor. If a significant interaction effect (Group × Time) is observed, simple main effects will be analyzed to determine differences between specific groups at each time point, with Bonferroni adjustments applied for multiple comparisons. A two-sided *p*-value < 0.05 will be considered statistically significant.

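### Three WOMAC subscales are each primary and each tested at two-sided 0.05, with no rule covering the three together; if any one suffices, the family-wise error is about 8–14%, depending on their correlation.

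*Protocol article*

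**What the plan says.** The three subscales are primary throughout. The abstract states: "The primary outcomes are the pain, stiffness and physical function subscales". The study design overview, Table 1 and the Primary outcome section list the same three, and the Analysis section fixes the time point: "primary outcomes for this study are defined as the changes from baseline to Week 12 in the three WOMAC subscales".

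The significance level is undivided wherever it appears. The Analysis section reads "All statistical tests will be two-tailed, with a significance level set at" p < 0.05. The Statistical analysis section also gives a two-sided 0.05, and the Sample size section has "Significance Level (α): Set at 0.05 (two-tailed").

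Multiplicity is addressed in two places, both under Statistical analysis. After a significant one-way ANOVA, "pairwise comparisons will be conducted using the Bonferroni correction to adjust for multiple testing". After a significant group-by-time interaction in the repeated measures ANOVA, simple main effects are examined "to determine differences between specific groups at each time point, with Bonferroni adjustments applied for multiple comparisons".

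The Sample size section uses one change in a WOMAC score at week 12. It names WOMAC pain, WOMAC physical function and the SF-36 physical component summary as the measures behind the calculation, and it draws the effect size from reported gains in proprioception and WOMAC function. It does not mention stiffness.

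**The concern.** Both Bonferroni steps work inside a single outcome: they adjust for three arms, or for arms at several visits. Neither adjusts for having three primary outcomes. The article therefore specifies its multiplicity method, and that method leaves out the primary family. It also does not say what pattern of results across the three subscales makes the trial positive.

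Read as written, a result on one subscale alone could be presented as a primary finding at the nominal 0.05. That includes stiffness, a two-item scale that plays no part in the sizing. The article expects its results to inform treatment guidelines, the subscales are self-reported, and participants know their allocation. What counts as success should therefore be fixed before data exist.

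**Working it through.** **Inputs from the protocol article.** Three primary subscales at week 12 (Analysis); two-sided 0.05 for each test (Analysis, Statistical analysis, Sample size); three arms of 40; f = 0.32; "Statistical Power: Set at 80% (0.80"); 15% dropout (Sample size).

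**Input not in the article.** The correlation r between subscales. It is an assumption, and the range 0 to 0.9 is shown.

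**Step 1: the plan's own figure.** Power comes from the noncentral F distribution with noncentrality N × f², numerator df 2, and denominator df N − 3 (N − 4 with one covariate). At f = 0.32 and alpha 0.05, 80% power needs N = 98, or 99 with equal arms. Allowing for dropout, 99 / 0.85 = 116.5, so 117, close to the stated 120. The sizing thus reproduces with one outcome at an undivided 0.05. It holds no allowance for three.

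**Step 2: family-wise error, independent subscales.** 1 − (1 − 0.05)³ = 1 − 0.857 = 14.3%. This holds for any three independent tests at 0.05, whichever omnibus test is used.

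**Step 3: family-wise error, correlated subscales.** This was simulated under the global null: 100,000 trials per setting, 40 per arm, equal pairwise correlation r, and a one-way F test at 0.05 on each subscale. The last column also requires at least one Bonferroni-adjusted pairwise contrast to be significant within a subscale whose omnibus test is significant, as the Statistical analysis section implies for a claim about a particular arm.

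| Assumed r | At least one omnibus test significant | Omnibus and an adjusted pair significant |
|---|---|---|
| 0 | 14.3% | 12.1% |
| 0.5 | 12.7% | 10.8% |
| 0.7 | 11.2% | 9.6% |
| 0.8 | 10.0% | 8.6% |
| 0.9 | 8.5% | 7.2% |

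A separate simulation gave 14.3%, 12.9%, 10.9%, 9.9% and 8.3% for the omnibus column, and 12.2% down to 7.1% for the last column.

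**Step 4: what correcting across three subscales does to power.** The first Holm step uses 0.05 / 3 = 0.0167. The evaluable number after dropout is 120 × 0.85 = 102. At f = 0.32:

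| Evaluable | Power at 0.05 | Power at 0.0167 |
|---|---|---|
| 102 | 82% | 68% |
| 120 | 88% | 77% |

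To restore 80% power at 0.0167, N = 127 evaluable is needed (129 with equal arms), and 129 / 0.85 = 151.8, so 152 randomised.

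These power figures take f = 0.32 as stated; its derivation is not examined here.

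**The case against.** The strongest reply has four parts.

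- **The analysis plan may settle it.** The Blinding section mentions a statistical analysis plan still to be finalised, and a rule for combining co-primary outcomes often sits there. This stands only in part. The article is not silent: it gives its multiplicity method, sets 0.05 for all tests and sizes the trial on that 0.05. A plan that split alpha would change those statements and lower the stated power.
- **No any-one rule is written.** This stands. A reader might infer that the article commits to claiming success on any single subscale, and so that its error rate simply is 10–14%. The documents do not support that: they state neither an any-one nor an all-three rule. Under an all-three rule no correction would be needed. The inflation is conditional on the any-one reading.
- **The size depends on the correlation.** This also stands. Zero correlation between three subscales of one questionnaire is hard to believe, so 14% is an upper bound under the any-one reading. A reader might infer an error two to three times nominal. At r = 0.9 it is 8.5 / 5 = 1.7 times for the omnibus tests, or 7.2 / 5 = 1.4 times with the pairwise requirement.
- **The article sometimes speaks of one primary outcome.** Statistical analysis and Analysis both use the singular, and the latter singles out knee pain at weeks 24 and 48 as secondary. That does not name a single primary, since the same section defines three.

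**Conclusion.** The point holds in conditional form. Three subscales are primary, each is tested at two-sided 0.05, and the planned Bonferroni steps do not reach across them. No hierarchy, split of alpha or all-three rule is stated. Followed as written, the plan leaves the error rate of the primary family uncontrolled.

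If one significant subscale is enough, that rate is about 8–14% for the omnibus tests, or about 7–12% if an adjusted pairwise contrast is also needed, against the intended 5%. The ranges rest on the any-one reading and on assumed correlations from 0.9 down to 0. Only near-perfect correlation would bring the omnibus figure close to 5%.

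**What to change.** **Preferred.** Before recruitment, name one WOMAC subscale at week 12 as the single primary outcome and make the other two secondary. The Sample size section does not identify one subscale without ambiguity, so the sponsor has to choose. That section rests its sizing on pain and physical function and its effect size on function, and it gives no basis for stiffness. Restate the abstract, the study design overview and Table 1, Statistical analysis, Primary outcome, Sample size and Analysis to match. The stated alpha then stands and no power is lost by splitting it. The cost is wording, plus giving up primary status for two subscales.

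**Alternative.** Keep all three. Apply Holm or a fixed testing order to the three week-12 omnibus tests at an overall 0.05, and test pairwise contrasts only within a subscale whose omnibus test has been rejected. The two procedures differ in cost:

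- **Holm:** the power statement must be rewritten. At f = 0.32 the first test, at 0.0167, has about 68% power with 102 evaluable (77% with 120), against 82% (88%) at 0.05. Holm relaxes the threshold after each rejection, so this is the most a subscale loses. Guaranteeing 80% at 0.0167 would take about 152 randomised instead of 120.
- **Fixed order:** the first subscale is tested at the full 0.05, but a failure there ends confirmatory testing of the others.

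The Study status and timeline section says that recruitment had not begun at submission and no data had been analysed, so either rule can still be prespecified cleanly.

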## Randomization and allocation concealment

To ensure the fairness and transparency of the allocation process, a computer-generated random sequence will be used to assign participants to the three intervention groups: Tai Chi, Baduanjin, and health education. The randomization sequence will be generated by an independent statistician who is not involved in participant recruitment or assessment.

Allocation concealment will be strictly maintained prior to enrollment. The randomization list will be kept in a secure, centralized system accessible only to the designated research coordinator responsible for enrollment. Until the moment of assignment, both the participants and the recruiting researchers will remain unaware of the upcoming group allocation to prevent selection bias. Participants will be randomly allocated to each intervention group with a target sample size of 40 participants per group.

Prior to randomization, all participants will undergo a detailed baseline assessment, including the pain, stiffness, and physical function subscales of the Western Ontario and McMaster Universities Osteoarthritis Index (WOMAC), as well as the Berg Balance Scale, 6-minute walk test, and SF-36 quality-of-life assessment. These baseline data will be used for subsequent statistical analyses to evaluate the effects of the interventions.

After allocation, participants will be officially enrolled into their respective study groups and begin the corresponding interventions. We acknowledge that due to the nature of these behavioral interventions, participants and instructors cannot be blinded to the group assignment after randomization. Therefore, rigorous measures have been implemented to blind outcome assessors and data analysts, as detailed in the following section. Throughout the study, we will closely monitor participants' adherence and intervention fidelity to ensure the accuracy of the results.

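### The primary analysis omits the baseline covariate that the sample size assumes, and the secondary covariates are chosen by baseline significance tests

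*Protocol article*

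**What the plan says.** All places are in the protocol article.

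- **Analysis, primary endpoint:** "The primary outcomes for this study are defined as the changes from baseline to Week 12 in the three WOMAC subscales".
- **Analysis, primary model:** intention-to-treat, "without adjustment for covariates, and with missing 12-week outcomes imputed as no change".
- **Analysis, secondary models:** "Secondary analyses will adjust for baseline characteristics that differ significantly by treatment group". Five are named: gender, initial pain severity, use of medication, duration of disease and the number of chronic conditions.
- **Statistical analysis:** for the primary outcome, "repeated measures ANOVA will be employed, with Group as the between-subject factor and Time as the within-subject factor". No covariate is named.
- **Sample size:** a three-group one-way ANCOVA, "adjusting for baseline values of the primary outcome (change in WOMAC score at week 12"), with f = 0.32, two-tailed alpha 0.05, power 80% and 15% dropout. This leads to 120 participants, 40 per arm.
- **Randomization and allocation concealment:** every participant has the three WOMAC subscales measured before randomisation.

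**The concern.** There are two separate faults.

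First, the trial is sized on a model that no section plans as the primary analysis. Statistical analysis and Analysis both leave the baseline score out as a covariate, although everyone has it. A raw change score subtracts the whole baseline. When the correlation between visits is below 1 this over-corrects, so a chance imbalance at baseline carries into the comparison through regression to the mean, and precision is lost. At stake is whether the planned test has the power claimed for it.

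Second, the secondary adjusted analysis admits covariates according to whether they differ significantly between arms. In a randomised trial such a difference arises by chance and says nothing about how strongly the variable predicts outcome, which is the reason to adjust. The secondary model therefore cannot be written down before the data are seen. A strong predictor such as initial pain severity will usually be left out.

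**Working it through.** **1. The stated sample size.** Inputs from Sample size: three groups, one covariate, f = 0.32, alpha 0.05, power 0.80. With a noncentral F (2 numerator df, noncentrality N·f²), 98 completers are needed, or 99 for equal arms. Allowing for 15% dropout: 99/0.85 = 116.5, so 117 (39 per arm), against 120 stated. The figure reproduces with rounding up. With 120 × 0.85 = 102 completers, the ANCOVA has 82% power.

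**2. Precision of the two models.** Let r be the baseline to week-12 correlation and assume equal SDs σ at both visits.

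- Variance of the change score: 2σ²(1 − r)
- Residual variance of the ANCOVA: σ²(1 − r²)
- Ratio, ANCOVA to change score: (1 − r²)/[2(1 − r)] = (1 + r)/2

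This gives 0.65, 0.75 and 0.85 at r = 0.3, 0.5 and 0.7. The document does not give r, so the range is an assumption.

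**3. Unequal SDs.** With k = SD(baseline)/SD(week 12), the ratio is (1 − r²)/(1 + k² − 2rk). At r = 0.5 and k = 0.8 it is 0.75/(1 + 0.64 − 0.80) = 0.75/0.84 = 0.89. In patient numbers, the change score costs 1/0.75 = 1.33 times as many at k = 1, but only 1/0.89 = 1.12 times as many at k = 0.8. A smaller baseline SD is plausible, because Study sample restricts entry to WOMAC pain 13 to 38 of 50 and total 50 to 150 of 240. If k exceeds 1, the loss is larger. The document does not give k.

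**4. Power with 102 completers, equal SDs.** The result depends on which SD f = 0.32 refers to.

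- *Reading A:* f is the baseline-adjusted effect, as an ANCOVA calculation implies. The change-score effect is then 0.32·√[(1 + r)/2].
- *Reading B:* f is on the change-score SD. The ANCOVA effect is then 0.32/√[(1 + r)/2].

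| r | Ratio | A: f unadjusted | A: power unadjusted (ANCOVA 82%) | A: completers for 80% (ANCOVA 98) | B: f with ANCOVA | B: power with ANCOVA (unadjusted 82%) |
|---|---|---|---|---|---|---|
| 0.3 | 0.65 | 0.258 | 63% | 148 | 0.397 | 95% |
| 0.5 | 0.75 | 0.277 | 69% | 129 | 0.370 | 92% |
| 0.7 | 0.85 | 0.295 | 75% | 114 | 0.347 | 88% |

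A ratio of 0.90 (r = 0.8) gives 78% under reading A and needs 108 completers. The k = 0.8 case in step 3, with ratio 0.89, lies close to this. If all 120 were followed up, unadjusted power under reading A would be 71%, 77% and 82% at r = 0.3, 0.5 and 0.7, against 88% for the ANCOVA.

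**5. The significance rule.** Each covariate tested at 5% is flagged in about 5% of randomised trials. For five independent covariates, at least one is flagged in 1 − 0.95⁵ = 23%.

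A simulation applied the rule to the baseline score alone: 20,000 runs, 34 per arm, both exercise arms shifted by 5/9 of a change-score SD. At r = 0.5, power was 64% unadjusted, 65% under the rule and 77% with a pre-specified ANCOVA, so the rule recovers almost nothing. Under the null, its type I error was 4.1% to 4.7% over r = 0.3 to 0.7, slightly conservative and not inflated.

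**The case against.** A reader might infer more than the document supports on several points.

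- **That the primary analysis disregards baseline.** It does not: the endpoint is a change, so each participant's baseline is subtracted, and the repeated measures model has Time as a factor. What is missing is baseline as a covariate.
- **That the primary test depends on the data or is biased.** It does not and is not. The Analysis section fixes it in advance with no covariates. Omitting a baseline covariate neither biases the comparison over randomisations nor inflates its type I error. Data-dependence is confined to the secondary adjusted analyses.
- **That the trial is certainly underpowered.** This holds only on reading A. Sample size does not say whether f = 0.32 is on the adjusted or the change-score SD, and on reading B the planned analysis already reaches about 82%.
- **That a third more patients are needed.** That figure requires r = 0.5 and equal variances. With the restricted entry range the loss may be much smaller.
- **That 77% of trials would adjust for nothing.** The 23% above assumes independent covariates and exactly five candidates. Pain severity, medication use, disease duration and comorbidity are unlikely to be independent, and the list is introduced as examples. The 5% per covariate is the safer statement.
- **That the randomisation section contradicts the plan.** Its remark that "These baseline data will be used for subsequent statistical analyses to evaluate the effects of the interventions" is met by a change score, so no contradiction follows.

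The covariate list might also be read as a fixed set. The condition attached to it, a significant difference between arms, rules that out.

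These objections limit the scope and size of the point. They leave standing the mismatch between the sizing model and the analysis models, and the significance-based selection rule.

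**Conclusion.** The point holds as one of efficiency and pre-specification, not of validity.

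The primary model omits the baseline covariate on which the trial was sized. The cost cannot be fixed exactly, because it rests on r, on the SD ratio and on the meaning of f, none of which the document gives. Over r = 0.3 to 0.7 with equal variances and 102 completers, the choice either leaves the planned test short of the stated 80% (reading A) or forgoes 6 to 13 percentage points of power above 82% (reading B). ANCOVA is at least as precise asymptotically in every case, so the baseline score is worth using on either reading.

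The secondary adjusted analysis is not a fixed analysis, and it selects covariates on a criterion unrelated to their prognostic value. This should be corrected, and Study status and timeline reports that at submission recruitment had not begun and no data had been analysed.

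**What to change.** - Make the primary model an ANCOVA for each WOMAC subscale at week 12, with the baseline value of that subscale as covariate for every participant. Bring Statistical analysis and Analysis into line with Sample size.
- State in Sample size whether f = 0.32 refers to the baseline-adjusted or the change-score SD, and the correlation assumed.
- In the secondary adjusted analysis, use a fixed set named in advance and drawn from the listed covariates, whatever their baseline p-values. A short prognostic set is enough. Where initial pain severity is the baseline WOMAC pain score, do not enter it twice in the pain model. Check that medication use still varies, since Study sample excludes recent drug treatment for knee osteoarthritis.
- Drop between-arm significance tests of baseline variables as a selection rule.

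The cost is a change of wording in the protocol or SAP. The baseline WOMAC scores are already scheduled for every participant, so the primary model needs no new measurement.
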